## Trial status

The trial has been registered with the Australian New Zealand Clinical Trials Registry. The registration number is ACTRN12619000474156, and the trial was registered on 21 March 2019. Recruitment is set to begin in Feburary 2020. The approximate date that the recruitment will be completed is 20 July 2020.

## Data Availability

Not applicable.

## Appendix

### Adverse events associated with THC and CBD

Adverse events will most likely occur within 1 h of administration of the medication but will often resolve within 48 h of treatment. Participants will report their adverse events to make sure the titration is appropriate for them.

Compared with how you normally feel, have you experienced a change in any of the symptoms described below in the last hour? Tick the most appropriate box below.

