#### Experimental phase

This phase of the study will take 16 weeks to complete. To minimise the risk of adverse events and variation in the maximum tolerated dose of CBM oil, each participant will receive one dose on the first and second days (2 pm) and two doses (9 am and 2 pm) for the reminder of both treatment cycles. A registered nurse will administer the dose along with a small meal (e.g., morning and afternoon tea), and the rate of titration will be monitored by the pharmacist to ensure it is appropriate for each individual. The participant will gradually receive an increased dose (titration) of the medication over several weeks, as shown in Table 1. During these weeks, the participant along with the care staff will record the presence of, and any change in, any potential adverse events that may be associated with the medication after the first dose, each afternoon when the dose is increased, and again on the final day of medication. If an adverse event is noted, the participant will revert to their previous best tolerated dose using the adverse events and safety protocol listed below.

**Table 1 Tab1:** Titration administration, including dose and number of sprays

Day(s)	Week	Dose administered (daily)		Number of spray(s) per dose	Adverse events recorded (time)
		9 am	2 pm		
**1**, 2	1	–	**2.5 m**g	1	3 pm
**3**, 4	1	2.5	2.5	1	
**5**, 6	1	2.5	**5**	1–2	3 pm
**7**, 8	1	5	5	2	
**9**, 10	2	5	**10**	2–4	3 pm
**11**, 12	2	10	10	4	
**13**, 14	2	10	**15**	4–6	3 pm
**15**, 16	2/3	15	15	6	
**17**, 18	3	15	**20**	6–8	3 pm
**19**, 20	3	20	20	8	
**21**, 22	3/4	20	**25**	8–10	3 pm
**23**, 24	4	25	25	10	3 pm

Adverse events will be recorded 1 h after drug administration on days of dose increase (days bolded) and on the last day of the treatment period

An upper limit of 50 mg/day of THC will be permitted in those who do not experience any adverse events from the medication. Once a participant has reached their maximum tolerated dose (or a total of 50 mg/daily of THC), they will continue to receive that dose until the cessation of the 6-week period. The placebo group will follow a similar titration process using the indicated volumes shown in Table 1. They will continue to receive an increase in the volume of medication until they record an onset of an adverse event, at which time they will continue to take that volume of placebo until the end of the 6-week placebo cycle.

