### Adverse events and safety protocol

An adverse events protocol will be put into place to minimise any potential harm or risks of receiving additional medication [14]. This will include participants reporting if they have experienced any adverse events 1 h after the increased dose has been administered (*see* Appendix). If moderate to severe adverse events are recorded (determined as ‘Somewhat worse’ (moderate) or ‘Much worse’ (severe) on the participant’s adverse event record) and these events have not ameliorated by the time for the next dose, the participant will receive the previous best tolerated dose. If the effects of the adverse event(s) have disappeared or become milder and do not interfere with the participant’s daily functioning or well-being, the registered nurse may increase the dose at the indicated rate. Recurrence of adverse events after two attempts to increase the dose will result in the participants remaining at their previous best tolerated dose for the remainder of the intervention period. A participant who experiences an adverse event will stay on the previous dose for another 2 days before the next dose is increased. At the beginning of the titration phase, a staff member at the aged-care facility will be vigilant in monitoring any acute adverse events such as dizziness, discoordination with a danger of falls and injury, and extreme fatigue. Any adverse events recorded will be reported to a facility line manager and will then be communicated to staff during shift changes.

Additional safety monitoring will be completed by a research nurse who will meet with each participant to discuss their adverse event records and measure their heart rate and blood pressure twice per week. In addition, the participant’s weight and non-invasive body composition measures such as lean body mass, bone mass, body fat percentage, and fat mass will be measured once per week using a portable scale. In addition, a nurse-led review will be completed 2 days into the washout periods to monitor the participant’s withdrawal symptoms once no more medication is being administered.

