**Table Taba:**

	No	Yes (tick box below)				
		Better	Somewhat better	Same as usual	Somewhat worse	Much worse
Drowsiness/fatigue						
Dizziness						
Dry mouth						
Sore throat						
Anxiety						
Nausea						
Memory decline or attention deficits						
Joy or euphoria						
Blurred vision						
Headache						
Paranoia						
Depression						
Lack of coordination						
Diarrhoea						
Appetite						
Sleep disturbance						

To be completed during the titration phase and following the last dose in each treatment arm

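### The printed adverse event record is a closed list of 16 symptoms with one-hour recall, no open row and no fall item, so unlisted events get no prompt and no grade on it

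*Protocol article*

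**What the plan says.** The Appendix prints the participant's adverse event record in full: question, rows, response boxes and footnote. The question is "Compared with how you normally feel, have you experienced a change in any of the symptoms described below in the last hour". Sixteen symptoms follow, each with a no box and a five-step scale from better to much worse. The footnote gives the schedule: "To be completed during the titration phase and following the last dose in each treatment arm". The footnote to Table 1 agrees, with events "recorded 1 h after drug administration on days of dose increase (days bolded) and on the last day of the treatment period".

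The intent stated under Experimental phase is wider. Participant and care staff are to record "any potential adverse events that may be associated with the medication".

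The section Adverse events and safety protocol defines moderate and severe as the two worst boxes "on the participant’s adverse event record". It also asks facility staff to watch, at the beginning of titration, for acute problems that include poor coordination with a risk of falls and injury. A research nurse is to meet each participant to "discuss their adverse event records and measure their heart rate and blood pressure twice per week".

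Safety is the first-named part of the primary aim (Aims), and the Data analysis section will test the proportion of adverse events in the CBM and placebo phases.

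**The concern.** The stated intent is open and the printed instrument is closed. An event outside the 16 rows has nowhere to be written on the form. Because severity is defined only by the form's boxes, such an event also has no grade under the stated rule. The clearest case is the fall: the protocol names it as a hazard, while the form lists dizziness and lack of coordination but not the fall itself.

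Participants have dementia, and the Discussion acknowledges short-term memory loss, so an event without a prompt is less likely to be volunteered. If unlisted events are recorded less completely than listed ones, the comparison of CBM and placebo phases gives an incomplete picture of safety.

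**Working it through.** No stated figure of the plan has to be reproduced here, and the sample size is not involved. The check is a count and a comparison of sections.

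**1. Rows on the form (Appendix).** From drowsiness or fatigue to sleep disturbance there are 16 symptom rows, 0 open rows and 0 fall or injury rows.

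**2. Where an unlisted event could go.**

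| Event | Row on form | Other route in the protocol | Graded? |
|---|---|---|---|
| Fall or injury | none | care-staff recording; staff vigilance at the start of titration; nurse contact | no |
| Fainting | none | the same, plus blood pressure readings | no |
| Palpitations | none | the same, plus heart rate readings | no |
| Hallucinations | none | NPI-NH domain, rated for frequency and severity on seven occasions | yes, as an outcome score |

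The first three can be noted elsewhere, but no route described gives them a prompt by name together with a grade, except that staff are alerted to the danger of falls. Hallucinations do not belong with them.

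**3. Forms per cycle (Table 1, participant with no holds).**
- Counting rows with a 3 pm time: days 1, 5, 9, 13, 17, 21 and 23, so 7. Adding the last day gives 7 + 1 = 8.
- Counting every bolded day: 1, 3, ..., 23, so 12. Adding the last day gives 12 + 1 = 13.

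**4. The stretch without a form.** On either count the last titration form falls on day 23 and the next on day 42.
- Days 24 to 41: 41 − 24 + 1 = 18 days, and 18/42 = 43% of the cycle.
- Longest interval between forms: 42 − 23 = 19 days.
- Dose over this stretch: 25 + 25 = 50 mg/day of THC, the permitted maximum.

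A participant whose titration is delayed by holds would have later dose increases, and so forms inside this window.

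**5. What else happens on days 24 to 41.** The four questionnaires are due on day 24 (Data collection). At two nurse contacts per week, 18/7 × 2 = 5.1, so about five contacts. At the weekly frequency given in the Abstract for heart rate and blood pressure, 18/7 = 2.6, so two or three. The Discussion places this monitoring in the treatment cycles generally and does not confine it to titration.

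**6. Dose protection.** Two rules require neither a listed symptom nor a grade: "If an adverse event is noted, the participant will revert to their previous best tolerated dose", and "A participant who experiences an adverse event will stay on the previous dose for another 2 days". An unlisted event that comes to notice can therefore still change the dose.

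**7. Scale of the form.** 8 × 2 cycles × 50 participants = 800 scheduled forms, or 13 × 2 × 50 = 1,300.

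**The case against.** The strongest reply is that the form is a titration tool. The Appendix gives its purpose as checking that titration suits the participant, and says events will most likely occur within an hour of dosing, which is when the form is filled in. The Data analysis section does not say that the phase comparison draws only on this form, and it plans no split by severity. A journal article may also leave a general adverse event log to the full protocol.

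Most of this stands, and it limits the point to the printed form and the grading rule tied to it. It does not remove the point. The form is shown in full, so its closed list is a stated choice and not a detail left out by the article.

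Three stronger readings are tempting, and the document does not support them:

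- *Unlisted events have no route at all.* Care-staff recording, staff vigilance, nurse contacts and vital signs are all described, and hallucinations are rated on the NPI-NH.
- *Almost all of the cycle is unobserved*, reached by dividing the few recalled hours by all hours of the cycle. That treats events as evenly spread over time, against the Appendix's statement on timing, and ignores the other contacts.
- *The comparison is biased towards CBM.* The same blinded form is used in both phases, and nothing in the document shows a direction.

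**Conclusion.** The point holds as a minor design weakness. The printed record gives unlisted events such as fainting, palpitations or a fall no prompt and no grade, although the protocol intends to record any potential event and itself names falls. For a participant who follows Table 1 without holds, no form is due on 18 of 42 days at the highest dose, while nurse contacts continue.

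Under-recording is possible. How many events would be missed cannot be computed from the document, and dosing is partly protected. The conclusion assumes that this form feeds the comparison of adverse event proportions at least in part, and that no general log outside the article already does the work. If such a log exists and is used equally in both phases, little of the point remains.

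**What to change.** Make two additions to the existing form.

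- **'Other (specify)'**, with the same severity boxes, subject to the same moderate/severe dosing rule and asked as 'since the last form'. Under the one-hour recall this row would still miss an event between forms.
- **'Fall or injury since the last form'**, yes/no, answered with care staff. A better-to-worse scale does not suit a fall.

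On the first form of each cycle, start the recall at that cycle's first dose, so that washout events are not credited to the second phase. Use both items identically in the two phases and count the entries in the planned comparison of adverse event proportions.

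The cost is two lines on about 800 to 1,300 forms, with no new visits. The downsides are some free-text coding and a recall of up to 19 days before the day 42 form. Care staff already record alongside the participant, which eases the recall but does not remove it.

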**Table Taba:**

	No	Yes (tick box below)				
		Better	Somewhat better	Same as usual	Somewhat worse	Much worse
Drowsiness/fatigue						
Dizziness						
Dry mouth						
Sore throat						
Anxiety						
Nausea						
Memory decline or attention deficits						
Joy or euphoria						
Blurred vision						
Headache						
Paranoia						
Depression						
Lack of coordination						
Diarrhoea						
Appetite						
Sleep disturbance						

To be completed during the titration phase and following the last dose in each treatment arm

## Abbreviations

BPSD: Behavioural and neuropsychiatric symptoms of dementia
CBD: Cannabidiol
CBM: Cannabinoid-based medicine
CMAI: Cohen-Mansfield Agitation Inventory
MMSE: Mini Mental State Examination
NPI-NH: Neuropsychiatric Inventory Questionnaire–Nursing Homes
QOL: Quality of life
QOL-AD: Quality of Life in Alzheimer’s disease
TGA: Therapeutic Goods Administration
THC: Delta-9-tetrahydrocannabinol
